## Abstract

**Background:**

Rapid conversion of atrial fibrillation (AF) to sinus rhythm may be achieved by the administration of class IA, IC and III antiarrhythmic drugs or vernakalant hydrochloride. However, that treatment may be related to potential pro-arrhythmia, lack of efficacy or the exceptionally high cost of a compound used. Antazoline is a first generation antihistaminic agent with chinidin-like properties. When administered intravenously, antazoline exerts a strong antiarrhythmic effect on supraventricular arrhythmia, especially on AF, facilitating rapid conversion to sinus rhythm. Despite a relative lack of published data antazoline has been marketed in Poland and widely used in cardiology wards and emergency rooms for many years due to its efficacy, safety and rapid onset of action within minutes of administration.

**Methods/design:**

A randomized, double blind, placebo-controlled, superiority clinical trial was designed to assess clinical efficacy of antazoline in rapid conversion of AF to sinus rhythm. Eligible patients will present AF lasting less than 43 hours, will be in stable cardio-pulmonary condition and will have no prior history of advanced heart failure or significant valvular disease. Long-term antiarrhythmic therapy is not considered an exclusion criterion. Subjects who fulfill selection criteria will be randomly assigned to receive intravenously either antazoline or placebo in divided doses and observed for 1.5 hours after conversion to sinus rhythm or after the last i.v. bolus. Primary end point will be the conversion of AF to sinus rhythm confirmed in an electrocardiogram (ECG) during the observation period. Secondary end points will be comprised of time to conversion and return of AF during the observation period. Special consideration will be given to the observation of any adverse events. A sample size of 80 patients was calculated based on the following assumptions: two-tailed test, a type I error of 0.01, a power of 90%, efficacy of placebo 5%, efficacy of antazoline 50% and 20% drop-out rate to fulfill the criteria of intention-to-treat analysis. Due to the presumed lack of statistical power, the secondary end points and safety endpoints will be considered exploratory.

**Clinical trials registry:**

ClinicalTrials.gov, NCT01527279

## Background

Atrial fibrillation (AF) is considered to be not only a medical but also a social problem. It is related to the elevated risk of thrombo-embolic events with a stroke being the most important and it adversely affects life expectancy and quality. The cornerstone of AF therapy is a long-term antithrombotic treatment followed by adequate rhythm or rate control [1,2]. The pharmacological cardioversion (CV) of AF to sinus rhythm (SR) may be achieved by administration of class IA, IC and III antiarrhythmic drugs: flecainide, ibutilide, dofetilide, propafenone or amiodarone [1,2]. Beta-adrenergic blocking agents are not considered suitable for pharmacological CV due to their low or lack of efficacy. Another drug recently introduced for rapid CV of AF is vernakalant [3-6]. Pharmacological CV may be related to potential pro arrhythmia, lack of efficacy or exceptionally high cost of a compound used.

So far there is no significant evidence of superiority of either rate or rhythm control strategies in terms of mortality, severe AF complication rates, worsening of heart failure quality of life of patients with AF. A hypothesis that deleterious effects of antiarrhythmic drugs may have offset the benefits of SR in those patients is seriously considered. Therefore a decision of SR restoration and maintenance for a long time should be patient-tailored and based on the individual patient’s history, symptoms and preferences [1].

Antazoline is a first generation antihistaminic agent with chinidine-like and anticholinergic properties. Antazoline prolongs action potential duration and lowers its amplitude, prolongs phase 0 duration, reduces phase 4 of resting potential and reduces excitability of cardiac tissue. Clinically, antazoline lowers the velocity of intraatrial conduction, prolongs the atrial refraction period and may improve atrioventricular conduction allowing fast ventricular response to supraventricular arrhythmias. The half-life of antazoline is considered to be about three hours with antiarrhythmic efficacy expiring after about one hour [7-9].

There are no widely known sound randomized clinical studies conducted to evaluate the antiarrhythmic effect of antazoline. Published studies were mainly single-arm clinical trials with no control group or a different series of cases where antazoline was administered either orally or intravenously in different doses and in different arrhythmias. These studies suggested high efficacy of antazoline in rapid conversion of AF to SR if administered intravenously up to the cumulated dose of 350 mg. Most adverse effects were observed after cumulated doses exceeding 250 mg and they were mainly comprised of mild hypotension, hot flushes and mild tachycardia. Antazoline can unmask the underlying sick sinus syndrome or atrio-ventricular block [7,8,10-27]. Moreover, antazoline has been used in clinical practice in Poland for many years due to its efficacy, safety and rapid onset of action within minutes of administration. According to the Summary of Product Characteristics**,** antazoline is indicated in the treatment of paroxysmal supraventricular tachyarrhythmias including AF and should be administered intravenously in a cumulative dose of 100 to 300 mg during 3 to 10 minutes under strict monitoring of ECG and arterial blood pressure and interrupted after conversion to SR.

The aim of this randomized, double blind, placebo-controlled, superiority clinical trial is to assess clinical efficacy of antazoline in rapid conversion of atrial fibrillation to sinus rhythm in patients with paroxysmal atrial fibrillation without significant valvular disease or advanced heart failure.

## Methods/design

The study protocol was approved by the local ethics committee and is in full compliance with the Declaration of Helsinki.

### Participants

All patients with AF lasting less than 43 hours reporting to the emergency room (ER) or clinical ward of our center will be considered for inclusion.

### Inclusion criteria

 – Written informed consent for participating in the study and written standard version of informed consent for cardioversion accepted at the Institute of Cardiology, Warsaw, Poland

 – Age 40 to 75 years

 – Potassium blood concentration over 3.5 mmol/l

 – Stable cardio-pulmonary state on enrollment

 – In case of unclear history of heart failure or suspicion of left ventricle damage echocardiography is indicated prior to enrollment

 – A long-term antiarrhythmic drug therapy is allowed

### Time window

The AnPAF Study is designed both for symptomatic and asymptomatic patients.

In symptomatic patients the self-reported onset of symptoms is considered when determining the time of AF episode. In symptomatic patients on long term antiarrhythmics or oral anticoagulants the self-reported onset of symptoms of a recent episode of AF is considered when determining the inclusion criteria.

In asymptomatic patients a medical documentation of SR within the last 43 hours must be available to enroll the patient (for example ECG strip).

In order to ensure patients’ safety in all ambiguous or controversial cases patients will not be considered for enrollment.

### Interventions

#### Both groups

Apart from the assigned drug the treatment of both groups will not differ at any time during the study.

Any patient fulfilling the inclusion criteria will be prepared to pharmacological CV in a standard way comprising the standard baseline 12-lead ECG, continuous ECG monitoring, periodic noninvasive blood pressure monitoring (BP) and iv line. The study drug or placebo will be administered intravenously in boluses by a nurse under supervision of the enrolling physician, both blinded to patient assignment. Both substances will be prepared in syringes by the study nurse unblinded to patient assignment. After administration the patient will be observed for 1.5 hour after the last dose with exit ECG and BP measure taken at the end of observation. Further treatment of the patient depends on the clinical state and follows current clinical guidelines.

#### Study group

Patients assigned to the antazoline group will be administered antazoline in boluses of 50 mg diluted to 10 cm^3^ every five minutes up to a cumulative dose of 250 mg or conversion of AF to SR. Drug administration will also be stopped in case of an adverse event (see Outcomes section) or conversion of AF to a different supraventricular arrhythmia. BP will be measured before every injection.

#### Control group

Patients assigned to the control group will be administered 0.9% saline in boluses of 10 cm^3^ every five minutes up to a cumulative volume of 50 cm^3^, conversion of AF to SR or in case of an adverse event (see Outcomes section) or conversion of AF to a different supraventricular arrhythmia. BP will be measured before every injection.

### Objectives

The purpose of the study is to assess clinical efficacy of antazoline in rapid conversion of AF to SR in patients with paroxysmal atrial fibrillation without significant valvular disease or advanced heart failure. Due to a presumed lack of statistical power, secondary end points and safety analysis will be considered exploratory.

### Outcomes

All clinical outcomes will be assessed by the enrolling physician and later adjudicated by an experienced cardiologist both blinded to patients assignment.

All safety outcomes will be assessed by the enrolling physician blinded to patient’s assignment. In order to provide maximum safety for the patient, a physician unblinded to patent’s assignment but not involved in the clinical outcomes assessment will be available at the study site at all times.

**Primary outcome:** conversion of AF to SR confirmed in standard 12-lead ECG during the observation period

**Secondary end points:** time to conversion; return of AF during observation period; serious adverse event defined as **every** adverse event requiring hospitalization or prolonged observation

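### The serious-adverse-event end point, read literally, leaves out a death during observation and a life-threatening event fully corrected within the planned 1.5 hours

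*Protocol article*

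**What the plan says.** The Outcomes section of the Protocol article lists three secondary end points: time to conversion, return of AF during observation, and serious adverse event. The last is defined as every "adverse event requiring hospitalization or prolonged observation". No other seriousness criterion appears anywhere in the article. The abstract is shorter still: "Secondary end points will be comprised of time to conversion and return of AF during the observation period", with no mention of serious adverse events, although it does promise special attention to any adverse event.

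The Safety endpoints section has a separate list. It includes BP below 90 mmHg, disturbed AV conduction, new complex ventricular arrhythmia and tachycardia above 180. It does not include death, and it grades none of its entries by seriousness.

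The Both groups section fixes the window: "After administration the patient will be observed for 1.5 hour after the last dose". After that, "Further treatment of the patient depends on the clinical state" and on current guidelines. The Objectives section states that "secondary end points and safety analysis will be considered exploratory".

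**The concern.** The definition is closed: it has two criteria and nothing to show that they are examples. The emphasised word 'every' widens the set of events considered, but each event must still meet one of the two criteria. Both criteria describe what happens to the patient afterwards. Neither describes how grave the event was. A patient who dies on the table needs neither admission nor longer monitoring. A patient whose life-threatening event is fully reversed and who leaves on time also meets neither criterion.

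What is at stake is the meaning of one reported count. The Background says that no widely known sound randomized studies have evaluated the drug's antiarrhythmic effect, so readers will look at the serious-event line with interest. That line should not rest on wording under which a death does not qualify.

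**Working it through.** No stated figure belongs to this end point, so the check is mainly a reading of the text.

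**The window.** The Study group section allows boluses of 50 mg every five minutes up to 250 mg, which is 250/50 = 5 boluses. The last is given at (5 − 1) × 5 = 20 minutes at the latest. Adding 90 minutes of observation gives at most 20 + 90 = 110 minutes from first bolus to exit ECG.

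**Can a grave but short-lived event occur in that window?** The Background says "Antazoline can unmask the underlying sick sinus syndrome or atrio-ventricular block", and also "The half-life of antazoline is considered to be about three hours with antiarrhythmic efficacy expiring after about one hour". A conduction or sinus-node event that appears and resolves within 110 minutes is therefore possible. The three-hour half-life points the other way, since the drug is still present when the window closes. The text makes such an event possible and says nothing about how often it occurs.

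**Applying the definition literally.**

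| Event | Meets either criterion? | Named under Safety endpoints? | Result |
|---|---|---|---|
| Rapid death during observation | No | No | Not counted as serious and not named anywhere as an outcome |
| Life-threatening AV block or complex ventricular arrhythmia, corrected, exit on time | No | Yes | Recorded, but without a seriousness label |
| Severe hypotension or tachycardia above 180, corrected, exit on time | No | Yes | Recorded, but without a seriousness label |
| Any of the non-fatal events above, patient kept longer or admitted | Yes | Yes | Counted as serious |

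The last row is the usual course for a patient who has just had a life-threatening reaction to an intravenous antiarrhythmic.

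**What one uncounted event would do to the report.** The only input is the 40 patients per group in the Sample size section. This shows the consequence if an event happens. It does not estimate how likely one is.

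- Counted: 1/40 = 2.5%. Exact (Clopper-Pearson) 95% limits: lower 1 − 0.975^(1/40) = 0.06%; upper 13.2%, the p that solves (1 − p)^40 + 40p(1 − p)^39 = 0.025.
- Not counted: 0/40 = 0%. Upper limit 1 − 0.025^(1/40) = 8.8%.

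**What does not move.** The sample size rests on 5% against 50% conversion, a two-sided type I error of 0.01, 90% power and 20% drop-out. None of these involves adverse events.

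**The case against.** The strongest reply is that the gap needs a strained reading. Prolonged observation is a low threshold. To escape it, a patient must have a life-threatening event, recover completely, and be released on time by clinicians who are told to act on the clinical state, with an unblinded safety physician on site. Most fatal events would first call for extended care and so meet the definition. No investigator would leave a sudden death out of a serious-event report. That is largely right, and it is why the gap is narrow. It still relies on investigators overriding the written rule, and they may not all do so in the same way.

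A second reply is that a journal article condenses a fuller protocol, which may carry wider seriousness criteria for safety reporting. It may. But the article does not leave this end point undefined. It states a definition, and that definition is what can be judged.

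A reader might go further and infer that deaths would go unrecorded, or that the trial has no proper safety reporting. The documents do not support either inference. The abstract promises attention to any adverse event, and the Safety endpoints list would still record several of the grave ones. What is missing is the seriousness classification and any mention of death by name. Nor can a probability be put on the gap. The relevant rate is that of fatal or life-threatening events that lead to neither admission nor longer observation. The documents give no such rate, and the Background describes mainly mild adverse effects.

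**Conclusion.** The point holds as a small but real defect in a stated definition. Taken as written, the serious-adverse-event end point does not count a death during observation, or a life-threatening event fully corrected within 1.5 hours of the last dose. The effect is confined to one exploratory secondary end point. If a single event fell through in the antazoline group, 1/40 would be reported as 0/40. The two exact intervals (0.06% to 13.2%, and 0 to 8.8%) overlap widely, so the loss is mainly one of clinical meaning and much less of precision. The conclusion rests on two assumptions: that the two criteria are meant to be exhaustive, as the wording indicates, and that no wider definition governs this end point in a document not shown. It is a clarification worth making, and it does not threaten the trial's main conclusion.

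**What to change.** Replace the definition in the Outcomes section with: *serious adverse event defined as every adverse event that results in death, is life-threatening, or requires hospitalization, prolonged hospitalization or observation beyond the planned 1.5 hours*. Naming prolonged hospitalization also helps for patients recruited from the clinical ward, whom the Participants section allows and for whom a need for hospitalization says little. Do not add a criterion based on urgent intervention. Unless it is defined, it could draw in hypotension that is managed routinely.

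Add one case report form field for the criterion met, so that the count under the present two criteria can still be reported beside the wider one. For patients already treated, a blinded assessor should complete the field from the existing records.

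The cost is a short amendment, since "The study protocol was approved by the local ethics committee" and the trial is recruiting, together with one form field and a record check on at most 80 patients. The downside is a slightly broader serious-event category. The sample size, alpha, power and primary analysis stay as they are.

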### Safety endpoints

 – BP <90 mmHg

 – Disturbances of atrio-ventricular conduction

 – Sustained supraventricular arrhythmia other than AF

 – New complex ventricular arrhythmia

 – Hot flush

 – Drowsiness

 – Headache

 – Nausea/ vomiting

 – Chest pain

 – Tachycardia >180’

 – Prolongation of QTc (Bazett’s formula) in comparison to baseline (in ms)

### Randomization

Randomization will be provided by the independent statistician using SAS.9.2 software, SAS Institute Inc., Cary, NC, U.S.A.. Permuted block randomization will be used with a block size (AB, BA) not known by the investigators. After eligible patients give informed consent a specific unique identifier will be assigned to the patients. Use of this randomization process ensures proper trial enrollment and promptly provides the statistician with the basic patients enrollment information needed to monitor enrollment performance.

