### Blinding

The study will be conducted in double-blind fashion. The patient, enrolling physician, nurse who administering the drug, and clinician reviewing the clinical outcomes will all be blinded to the treatment. The statistician, study nurse who prepares the syringes and clinician involved in safety control will be unblinded to the patient’s assignment.

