## Statistical methods

### Sample size

The clinical efficacy of antazoline was assumed using data derived from Srzednicki *et al.* 1990 [8], the most credible publication available. Assumption of 50% efficacy in AF conversion is conservative, since the authors reported efficacy over 70% in doses not exceeding 250 mg of antazoline. Assumption of 5% efficacy of placebo was derived from studies over vernakalant [3-6]. Using a two-tailed test, a type I error of 0.01, a power of 90% and a 20% drop-out rate to fulfill the criteria of intention-to-treat analysis, we calculated that we need 80 patients, 40 in each group, to show the superiority of antazoline over placebo.

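### Fixed blocks of two, printed in the article while the trial recruits, weaken allocation concealment

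*Protocol article*

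**What the plan says.** All references are to the protocol article.

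- **Randomization:** "Permuted block randomization will be used with a block size (AB, BA) not known by the investigators". An independent statistician generates the list. No second block size and no stratification factor is given.
- **Participants:** recruitment is at one centre, from patients "reporting to the emergency room (ER) or clinical ward of our center will be considered for inclusion".
- **Sample size:** "we calculated that we need 80 patients, 40 in each group". The assumed conversion rates are 50% on antazoline and 5% on placebo.
- **Allocation concealment** and **Implementation:** allocations are held in numbered sealed envelopes. The study nurse opens each one once the patient has been included, then prepares the syringes and hands them to the enrolling physician and the administering nurse.
- **Blinding:** "The statistician, study nurse who prepares the syringes and clinician involved in safety control will be unblinded". The patient, the enrolling physician, the administering nurse and the clinician who reviews outcomes are blinded.
- **Outcomes:** the enrolling physician assesses clinical and safety outcomes. An unblinded physician who takes no part in assessing clinical outcomes is always available at the site.
- **Trial status:** the trial is recruiting.

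**The concern.** The sentence on block size undoes its own safeguard. It relies on investigators not knowing the size and then prints the two permutations, which identify it, in an article that appears during recruitment.

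Two is the smallest possible 1:1 block, so one known or guessed assignment determines the next. A sealed envelope hides its contents only as long as they cannot be worked out in advance. Selection bias acts before the envelope is opened, when someone decides whether to enrol the next patient. Several eligibility criteria need judgement, such as a stable cardio-pulmonary state, clinically significant heart failure and the self-reported onset of symptoms. If the expected arm influenced those decisions, the two groups could differ at baseline in ways that no later analysis can fully repair. Blinded adjudication of the ECG would not help, because it protects the reading of the outcome and not the choice of who entered.

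**Working it through.** **The plan's own figure.** Inputs from the Sample size section are p1 = 0.50, p2 = 0.05, two-sided alpha 0.01, power 90% and drop-out 20%. The normal-approximation formula for two proportions with continuity correction gives 31 per arm. Allowing for drop-out, 31 / 0.80 = 38.75, so 39 per arm and 78 in total, within two patients of the stated 80. The sample size is not at issue. It supplies the count of 80 and the two rates used below.

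**Step 1: block size.** A 1:1 block of length two has exactly two orders, AB and BA. One centre and no stated strata mean one running sequence, and 80 / 2 = 40 pairs.

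**Step 2: someone who knows past assignments.**
- Second allocations fixed by the first: 1 in each of 40 pairs = 40 of 80 (50%).
- Correct guesses overall: (0.50 + 1.00) / 2 = 75%, or 60 of 80, against 40 of 80 by chance.

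**Step 3: a blinded enroller who uses conversion alone.** This assumes that the enroller knows where the pair starts and how its first patient responded. The first patient is equally likely to be in either arm.
- P(first patient converts) = 0.5 × 0.50 + 0.5 × 0.05 = 0.275, about 11 of 40 pairs.
- After a conversion, P(first was on antazoline, so second is placebo) = 0.50 / (0.50 + 0.05) = 91%.
- After no conversion, P(first was on placebo, so second is antazoline) = 0.95 / (0.95 + 0.50) = 66%.
- P(second arm guessed correctly) = 0.5 × (0.50 + 0.95) = 72.5%.
- Over all allocations: (0.50 + 0.725) / 2 = 61%, or about 49 of 80.

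**Step 4: sensitivity to the assumed rate.** The Sample size section calls 50% conservative and mentions a published rate above 70%. At 70% against 5%, the second arm is guessed correctly 0.5 × (0.70 + 0.95) = 82.5% of the time, and all allocations (0.50 + 0.825) / 2 = 66%. If both arms converted equally often, conversion would carry no information and the figure would be 50%.

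**Step 5: other block sizes.** The observer knows all past assignments. For fixed blocks the observer also knows the size; for mixed blocks the guess uses only the running imbalance.

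| Scheme | Fixed in advance | Guessed correctly |
|---|---|---|
| Fixed 2 | 50% | 75% |
| Fixed 4 | 33.3% | 70.8% |
| Fixed 6 | 25% | 68.3% |
| Fixed 8 | 20% | 66.6% |
| Random mix of 4 and 6 | not calculated | about 69% (simulation) |

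The fixed-block rows come from enumerating every permutation. The fall in guessability is modest. The larger gain from varying sizes is that an observer can no longer generally be sure where a block ends.

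**The case against.** The strongest reply is that those who know assignments with certainty do not enrol. The nurse opens the envelope only after inclusion, the enrolling physician is blinded, and the unblinded physician is a safety back-up outside clinical outcome assessment. This stands. The documents do not expressly bar the safety physician from enrolling, but nothing assigns that task. A reader might infer that every second allocation is known at the point of enrolment. The text does not support that, because a leak or some influence on the enroller would be needed.

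The 91% is also selective. It applies in 27.5% of pairs, and in the other 72.5% the guess is right 66% of the time. Both figures require knowledge of the block boundary and of the previous patient's outcome. Patients come from an emergency room and a ward, and the article does not say that one physician enrols consecutive patients. This stands too, so the 61% belongs beside the 72.5%. Side effects such as hot flush or drowsiness could add clues, but the documents give no rates from which to quantify them.

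Third, inference from conversion works only if the drug works, so this route alone could distort a real effect but not create one. That is correct for this route. It does not cover leaks or unmasking through side effects.

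Finally, a reader might take the rule that "in all ambiguous or controversial cases patients will not be considered for enrollment" as a general licence to turn patients away. It stands in the Time window section, as a safety rule tied to uncertain onset of the arrhythmia. The room for judgement lies in the other eligibility criteria.

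**Conclusion.** The point holds as a weakness in concealment that should be fixed. The article specifies blocks of two, and printing the pattern during recruitment contradicts the statement that investigators do not know it.

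In size, 40 of 80 allocations are fixed for anyone who knows the preceding assignment. For a blinded enroller with the boundary and the previous outcome, second allocations are guessed correctly 72.5% of the time and all allocations about 61%, against 50% by chance. These last figures rest on the article's 50% and 5% and on conversion as the only clue.

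They measure guessability, not bias. A reader might infer that selection took place or that the efficacy comparison is invalid. The documents do not show this, and no shift in the conversion difference or in the type I error has been calculated. The primary outcome is ECG-confirmed and adjudicated blind, and the assumed difference is 45 percentage points. The vulnerability is nevertheless avoidable, and an unstratified single-centre trial gains little from blocks this small.

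**What to change.** From the next completed pair, the independent statistician issues a new list for all unused envelopes, with larger, randomly varying block sizes. The sizes are held in a document that site staff cannot see, and the protocol says only that block sizes vary. Deleting the AB/BA pattern from site documents would not be enough, because publication cannot be undone. A new list makes the published pattern irrelevant to the patients still to be enrolled.

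The cost is a new list, new envelopes and a possible final imbalance of a few patients, at most half of the largest block. The benefit depends on how many envelopes remain unused, which the article does not say. Allocations already made are unaffected, and the report should state when the scheme changed.
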